### Plans for collection, laboratory evaluation and storage of biological specimens for genetic or molecular analysis in this trial/future use

We have no plans to collect or store biological specimens in this trial.

### Outcomes

#### Primary outcome measures

Primary outcome of this study is the incidence of POCD in the two groups during 7 days after surgery (or before leaving hospital), which was evaluated by *Z*-score (detail in the “Statistical analysis” section).

#### Secondary outcome measures

Secondary outcomes comprise the following:
POCD incidence in the two groups 1 month after surgery, which was evaluated by Telephone Interview for Cognitive Status—modified (TICS-m).POCD incidence in the two groups 6 months after surgery, which was evaluated by TICS-m.POCD incidence in the two groups 1 year after surgery, which was evaluated by TICS-m.Incidence of post-operative delirium in the two groups after surgery, which was evaluated by Confusion Assessment Method (CAM).

### Participant timeline

Figure 1 presents the schedule for enrolment, interventions, assessments and visits for participants.

Cognitive function will be assessed 1 day before surgery, in the first 7 days or before leaving hospital and at 1 month, 6 months and 1 year after surgery.

The evaluation of cognitive function will also include Visual Reproduction, Stroop Colour and Word Test (STROOP), Digit Span Test, Digit Symbol Substitution Test, Colour Trail Test 1 and Colour Trail Test 2.

Post-operative delirium will be assessed using the Confusion Assessment Method (CAM). The CAM includes acute onset, inattention, disorganised thinking and abnormal consciousness. The diagnosis of delirium by the CAM requires the presence of features 1 and 2 and either 3 or 4. Table 2 presents the specific content.

**Table 2 Tab2:** Specific content of the Confusion Assessment Method

The Confusion Assessment Method (CAM)	
Feature 1	Acute change in mental status with a fluctuating course Is there evidence of an acute change in mental status from the patient’s baseline? Did this behaviour fluctuate during the past day, that is, tend to come and go or increase and decrease in severity? This feature is usually obtained from a family member or nurse and is shown by positive responses.
Feature 2	Inattention Do the patients have difficulty focusing attention, for example, being easily distractible, or having difficulty keeping track of what was being said?
Feature 3	Disorganized thinking This feature is shown by a positive response to the following question: Was the patient’s thinking disorganized or incoherent, such as rambling or irrelevant conversation, unclear or illogical flow of ideas, or unpredictable switching from subject to subject?
Feature 4	Altered level of consciousness Overall, how would you rate this patient’s level of consciousness? (alert [normal], vigilant [hyperalert], lethargic [drowsy, easily aroused], stupor [difficult to arouse], or coma [unarousable])

The diagnosis of delirium by CAM requires the presence of features 1 and 2 and either 3 or 4

Long-term cognitive function will be assessed using a modified version of the Telephone Interview for Cognitive Status—modified (TICS-m) at 1 month, 6 months and 1 year after surgery. TICS-m has been used to screen for dementia and mild cognitive impairment. TICS-m scores range from 0 to 48, with higher scores indicating better function.

Evaluators will comprehensively assess the status of the patients according to their medical history, clinical observation, current psychiatric examination and information provided by family members, especially care providers [22].

### Sample size

In the previous study, we found that the POCD incidence in the elderly patients undergoing orthopaedic surgery is about 25% [20]. The anticipated effect size of donepezil is 50%. That means the power analysis for the primary outcome of POCD prevalence assumes a reduction from 25 to 12.5%. The results of a conventional analysis to detect differences in proportions (POCD) between the intervention and control groups, using PASS19.0, led to a total of 300 patients with a 1:1 randomisation, given a power of 1 − *β* = 0.80 and a two-side α level of 5%. Assuming a dropout rate of 10%, this results in a requirement of about 360 total patients.

### Allocation masking

This study is planned to follow a double-blinded method. In all cases, the investigator, intraoperative attending anaesthesiologist, evaluator, data analyser and patient will not be aware of the treatment allocation, as the medication will be encapsulated and provided by an independent nurse.

### Unblinding procedures

In the event of a medical emergency, which requires identification of an individual patient’s treatment, the investigators will be permitted to open the respective emergency envelope. A justification must be documented in the patient’s medical record and in the case report form (CRF). Serious adverse events will be collected and recorded for further analysis at the end of the trial, and investigators will explore the correlation between these events and patients’ healthcare records.

### Plans for communicating important protocol modifications to relevant parties

All changes to the study protocol will be reviewed by the ethical committee, which will be reported to the sponsor, participating care providers and investigators.

### Composition of the data-monitoring committee, its role and reporting structure

We have not considered there to be a need for a data-monitoring committee.

### Interim analyses

No formal interim analysis of the primary and secondary outcomes is planned.

### Frequency and plans for auditing trial conduct

We have no plans for auditing trial conduct in this investigator-initiated pragmatic trial.

### Data management

All patient data collected during this clinical study will be entered and/or filed in the respective patient’s CRF. The patient’s study participation must be documented appropriately in the patient CRF with study number, subject number, date of subject information and informed consent and date of each visit. Source data should be filed according to the GCP guidelines. The data manager will be responsible for data processing, according to the sponsor’s standard operating procedures. and will conduct regular monitoring to ensure that the dates are adequate, accurate and complete. Database lock will occur only after the completion of quality assurance procedures.

### Statistical analysis

Statistical analysis will be conducted using SPSS 20.0 (IBM Inc., Armonk, NY, USA). Continuous variables will be analysed using the unpaired *t* test or Mann–Whitney *U* test. Categorical variables will be analysed using the *χ*^2^ test, continuity correction *χ*^2^ test or Fisher exact test. The definition of POCD is determined using the *Z* score recommended by the International Study of Post-operative Cognitive Dysfunction studies [23]. We will compare the patients’ preoperative with post-operative scores 1 week later and divide the result by the standard deviation of the preoperative score of all patients to obtain a *Z* score for each individual test. Patients will be regarded as developing POCD if the *Z* score is ≥ 1.96 on ≥ 2 individual cognitive tests. A *P* value of < 0.05 will be considered statistically significant. The statistical code generated during the current study will be available from the corresponding author on reasonable request after the trial is completed.

### Methods in analysis to handle protocol non-adherence and any statistical methods to handle missing data

The statistical analysis will be conducted on an intention-to-treat (ITT) basis. The analyses of the outcomes will be analysed as randomised, regardless of protocol adherence. All variables will be screened for frequency and type of missingness. Multiple imputation will be used if missingness is above 5% in any variable. In the case of missing data and imputation, complete case analysis will be performed as a sensitivity analysis.

### Dissemination plans

The study results will be disseminated via articles published in peer-reviewed journals.

### Additional consent provisions for collection and use of participant data and biological specimens

No ancillary study is planned, and we have no plans to collect additional participant data or biological specimens outside of what is mentioned in this protocol.

### Adverse event reporting and harms

Donepezil, a first-line drug for AD, may cause some minor adverse effects but is generally well tolerated. We will evaluate any harm from the intervention and there is also a commentary section in the study-specific CRFs where researchers can report allocation violations or any unexpected side-effects from allocated intervention. We will collect all the expected and unexpected drug-related adverse events non-systematically and report all the harms in trial publications.

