#### Recruitment and informed consent

Figure 1 presents the schedule of the major study events for each study visit. Elderly patients who are scheduled to undergo orthopaedic surgery will be included in this study. This study is approved by the Ethics Committee of Ren Ji Hospital, Shanghai Jiao Tong University School of Medicine. Surgery will be performed within 2 days after the screening process. Designated doctors will explain this trial to interested potential participants in detail and provide them with the informed consent form. Participants are given at least 24h to decide whether they wish to participate in this trial. The informed consent form will be signed by the participant or his/her trustee or guardian and may be withdrawn at any time during the trial. Written informed consent and the patient’s baseline data will be obtained before randomisation. Moreover, participants are encouraged to contact the research team if they have any health concerns during the trial. Recruitment and consenting of study participants by the members of the research team is in-line with good clinical practice (GCP). During the clinical trial, the researchers will immediately report any serious adverse events occurring in the subjects, whether related to the drug under study or not, to the director in charge of the clinical trial of the research institution and contact [name] or [name].

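### Non-serious adverse events are collected unsystematically and only if thought drug-related, which conflicts with the protocol's promises on harms and with its own rule for serious events

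*Protocol article*

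**What the plan says.** The section on adverse event reporting and harms makes two general promises. It opens the first with "We will evaluate any harm from the intervention" and mentions a free-text area of the case report form as a further place for unexpected side-effects. It then sets the collection rule and the second promise in one sentence: "We will collect all the expected and unexpected drug-related adverse events non-systematically and report all the harms in trial publications".

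Serious events are handled elsewhere and differently. Under Recruitment and informed consent, "the researchers will immediately report any serious adverse events occurring in the subjects, whether related to the drug under study or not". Under Unblinding procedures, "Serious adverse events will be collected and recorded for further analysis at the end of the trial".

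Three other places bear on the point:
- Allocation masking states that "the investigator, intraoperative attending anaesthesiologist, evaluator, data analyser and patient will not be aware of the treatment allocation".
- The data-monitoring section states "We have not considered there to be a need for a data-monitoring committee".
- The primary and secondary outcome lists contain cognitive dysfunction and delirium, and no harm outcome.

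**The concern.** The harms sentence contains its own conflict. Events that nobody attributes to the drug, or that nobody happens to mention, are not recorded and so cannot be reported later. No analysis plan can recover them. This is a stated rule, not detail left out because an article is short.

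The relatedness filter also discards what the design is good at. After joint replacement under general anaesthesia, many symptoms have an obvious surgical or anaesthetic explanation. A clinician asked about one patient may reasonably put an event down to surgery even when the drug has raised its frequency. Comparing randomised arms needs no such judgement.

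At stake is the safety conclusion. The section starts from the premise that donepezil is generally tolerated well. If the trial records few non-serious events, the publication may repeat that premise from data with little ability to challenge it. The primary efficacy result is not affected.

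**Working it through.** **Step 1: the two rules side by side (protocol article).**

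| | Non-serious events | Serious events |
|---|---|---|
| Section | Adverse event reporting and harms | Recruitment and informed consent; Unblinding procedures |
| Relation to drug | Must be drug-related | Irrelevant ("whether related to the drug under study or not") |
| Mode | Not systematic | Immediate report, recorded for end-of-trial analysis |
| Promise attached | Evaluate any harm, report all harms | Further analysis |

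The wider promise is attached to the narrower collection rule. The protocol gives no reason for the difference.

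**Step 2: what under-capture does.** The plan states no harm rate and no power for harms, so there is no figure to reproduce. The following is an illustration.

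Inputs:
- n = 180 per arm, from about 360 patients at 1:1 (Sample size; Allocation).
- Two-sided 5% level (Sample size).
- True event rates of 20% on donepezil and 10% on placebo. These are assumptions and have no source in the documents.
- A fraction s of events is captured, equal in both arms. This is also an assumption, made plausible by the blinding.

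Observed rates are a = 0.20s and b = 0.10s. The ratio a/b = 2 does not depend on s. The difference is 0.10s, so the apparent excess falls from 10 points at s = 1 to 5 points at s = 0.5 and 3 points at s = 0.3.

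Normal-approximation power, with m = (a + b)/2:

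power = Φ{ [ (a − b)√n − 1.96√(2m(1 − m)) ] / √(a(1 − a) + b(1 − b)) }

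- s = 1: (0.10 × 13.416 − 1.96 × 0.5050)/0.5 = (1.342 − 0.990)/0.5 = 0.704, power 0.759.
- s = 0.5: (0.05 × 13.416 − 1.96 × 0.3725)/0.3708 = (0.671 − 0.730)/0.3708 = −0.160, power 0.437.

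Exact power of the Pearson chi-square test, by summing the binomial probabilities of all outcomes that reject, agrees closely:

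| Capture s | Observed rates | Approximate power | Exact power |
|---|---|---|---|
| 1 | 20% vs 10% | 0.759 | 0.768 |
| 0.75 | 15% vs 7.5% | 0.616 | 0.623 |
| 0.5 | 10% vs 5% | 0.437 | 0.441 |
| 0.3 | 6% vs 3% | 0.278 | 0.276 |
| 0.25 | 5% vs 2.5% | 0.238 | 0.235 |

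With assumed rates of 15% versus 5%, approximate power is 0.889, 0.773, 0.586 and 0.329 at s = 1, 0.75, 0.5 and 0.25. The level changes but the pattern does not.

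**Step 3: the loss expressed as precision.** The standard error of the log relative risk is √[(1 − a)/(na) + (1 − b)/(nb)].

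- s = 1: √(0.8/36 + 0.9/18) = 0.269. At the expected counts the 95% interval around 2.0 is 1.18 to 3.39.
- s = 0.5: √(0.9/18 + 0.95/9) = 0.394. The interval is 0.92 to 4.33.

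The same true doubling is distinguishable from no effect in the first case and not in the second.

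**The case against.** There is a serious case on the other side, and much of it limits how far the point goes.

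- **Serious events.** A reader might infer that the filter applies to all adverse events. It does not. Serious events are reported regardless of relation and recorded for analysis, so they can be compared by arm.
- **Inability to compare.** A reader might infer that harms cannot be compared at all. The documents do not support this. Investigator, evaluator and patient are blinded, so nothing suggests that capture differs by arm, and stratifying randomisation by centre should balance site differences. Equal under-capture leaves the relative risk intact in expectation. The loss is in absolute rates, precision and power.
- **A broken promise of comparison.** The protocol promises to evaluate and report harms. It nowhere expressly promises a donepezil-placebo comparison of them.
- **Route of recording.** The free-text area is described as an additional place for entries, so it is not shown to be the only route. Expected drug-related events are also within the stated collection.
- **Missing safety record.** Having no data-monitoring committee does not make the case report form the sole safety record. Such a committee reviews data and does not create them, and serious events also go to the director in charge.
- **Feasibility.** No daily in-hospital study contact is described, no length of stay is given, and the schedule figure is not shown. Daily questioning cannot be assumed to be free.

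All of these stand. None of them removes the stated filter, the stated lack of system, or the mismatch with the promises in the same section.

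**Conclusion.** The point holds for non-serious adverse events. As written, the collection rule cannot deliver an evaluation of any harm or a report of all harms, and it is inconsistent with the protocol's own rule for serious events. That conclusion rests on the text alone.

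The size of the consequence is only illustrative. Under the assumed 20% versus 10%, with equal capture in both arms, losing half the events takes power from about 77% to about 44% and halves the apparent excess. The true rates and the true capture fraction are unknown. The fair conclusion is that a statement of good tolerability from these data would be weakly supported. It would be wrong to conclude that the trial can say nothing about harms. The change is worth making because it is cheap and bears on the benefit-harm conclusion.

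**What to change.** Reconcile the harms section with the serious-event rule under Recruitment and informed consent. Replace the restriction to drug-related events gathered without a system by three statements:

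1. All adverse events are recorded regardless of suspected relation to the study drug. An opinion on relation may still be noted, but it does not decide whether the event is recorded.
2. The same fixed questions are asked in both arms at contacts already in the protocol: the 7-day or discharge assessment and the 1-month telephone interview, plus in-hospital study contacts where these already take place.
3. Counts are reported by randomised arm.

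The cost is a short added form and a little more data entry. Because the questions use existing contacts, no new visit is required. If the trial team wanted daily in-hospital questioning, it would first have to check whether such contacts exist.

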### Provisions for posttrial care

If participants are injured due to this study, in case of damage related to clinical research, they will get free treatment.

## Discussion

POCD is generally believed to indicate the degeneration of the central nervous system and the decline of nervous system function induced or aggravated by anaesthesia, surgery and other factors. A number of animal studies have shown that surgery has different effects on the cognitive function of animals of different ages [24, 25]. Our previous studies have also shown that adult mice and aged mice respond differently to isoflurane anaesthesia. The learning and memory ability of adult mice can be improved under repeated isoflurane anaesthesia [26], but the opposite is true for elderly mice. After isoflurane anaesthesia, learning and memory ability were shown to decrease significantly [18, 19]. We noticed that the central cholinergic state is different between adult mice and elderly mice and that the number of central cholinergic nerves in elderly mice decreased significantly. Before the age of 40 years, the activity of the central cholinergic system is continuously enhanced in healthy individuals, but it gradually degenerates after 40 years of age until the end of life [12]. The central cholinergic nervous system plays an important role in learning and memory as well as against central nociceptive responses. Studies have shown that nicotine or cholinesterase inhibitors can counteract cognitive impairment caused by AD [27, 28]. Additionally, in vitro studies have shown that nicotine can antagonise the neurotoxicity mediated by N-methyl-D-aspartate and β-amyloid protein [29]. Moreover, nicotine can reduce neurologic damage, behavioural changes and brain injury caused by stroke, Parkinson‘s disease in learning and memory [30–33]. The degeneration of the central cholinergic system that results from ageing is an important cause of cognitive dysfunction in elderly animals.

### Trial status

Trial registration: ClinicalTrials.gov, NCT04423276. Registered on 14 June 2020.

The protocol version is 1.1, which was approved in January 2020. This study started in June 2020, and the recruitment phase will last until December 2021.

## Data Availability

The participant-level data set cannot be made publicly available because of Chinese data protection rules and regulations. The statistical code is available upon request.

## Abbreviations

POCD: Post-operative cognitive dysfunction
AD: Alzheimer’s disease
ChAT: Choline acetyltransferase
GCP: Good clinical practice
STROOP: Stroop colour and word test
CAM: Confusion assessment method
TICS-m: Telephone interview for cognitive status—modified
CRF: Case report form
